### Sample size and power calculations

For practical reasons, we expect to be able to include 14 to 20 aged care settings, with a maximum of 132 DSI seniors and their nurses. Improvement in either one of the two social participation scales (one scale for hearing-related social participation, and one general scale for social participation), is considered a success; study success is defined as a statistically significant difference on either HHQ or ACS. The enrolment of 14 to 20 settings will enable us to detect an effect size of 0.7 or larger with 80% power on either HHQ or ACS (or equivalently stated, a precision (half-width of the 95% confidence interval for the estimate) of 0.36 standard deviation (SD)), based on the following reasoning: (1) Randomization is at the level of the aged care setting to avoid contamination that may arise should control group nurses come into contact with DSI senior nurses in the intervention group. (2) Uncorrected for clustering, a sample size of 32 per group is needed for the mentioned effect size and power (or equivalently, the stated precision). (3) Given a prevalence of 20% and accounting for low participation rates as found in most studies of very aged and medically compromised seniors, and an average size of a setting (100 to 200 seniors), we expect to recruit five to ten DSI seniors per setting. Typically, a nurse at each setting will coach one to two seniors, so that five nurses from one setting will be involved. Thus, seniors are nested within nurses within aged care settings. To account for this clustering (assuming an intra-nurse correlation between seniors of at most 0.3 and an intra- setting correlation between nurses of at most 0.10), the sample size has to be increased by a factor between 1.12 (if each setting has five nurses each with one senior) and 1.54 (if each setting has five nurses each with two seniors) [37]. In order to allow for an expected 25% dropout, the sample size per group needs to be between 48 and 66, which comes down to between 20 and 14 settings in total. For simplicity of recruitment, we aim to include 132 seniors.

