### Statistical methods

Descriptive statistics (mean standard deviation or median and interquartile range) will be used to describe the baseline characteristics of the aged care setting and of the seniors. We will use a linear mixed model to analyze the outcomes and to account for clustering of seniors within nurses within the settings and for repeated measurements. The influence of relevant/prognostic characteristics of aged care setting/seniors on the outcomes will also be investigated by including these as covariates.

The analysis will be based on all the resulting data using the intention-to-treat principle. Moreover, a per protocol analysis and a regression analysis with the adherence to intervention protocol (see below) will be performed to assess the influence of compliance. For all tests, significance will be tested using two-sided tests with an alpha level of .05.

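### The stated precision of 0.36 SD is not equivalent to 80% power at 0.7 SD: with 32 per group the 95% interval for the between-arm difference has a half-width of about 0.49 to 0.50 SD

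*Protocol article*

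**What the plan says.** All of this stands in the Sample size and power calculations section of the protocol article, apart from the significance level.

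- The trial is sized to "detect an effect size of 0.7 or larger with 80% power on either HHQ or ACS".
- In the same sentence this is restated, as an equivalent, in terms of precision: "a precision (half-width of the 95% confidence interval for the estimate) of 0.36 standard deviation (SD").
- Step (2) of the reasoning repeats the equivalence before any allowance for clustering: "a sample size of 32 per group is needed for the mentioned effect size and power (or equivalently, the stated precision").
- Step (3) applies the clustering allowance, "the sample size has to be increased by a factor between 1.12" and 1.54, and then the allowance for loss to follow-up ("In order to allow for an expected 25% dropout"), with the result that "the sample size per group needs to be between 48 and 66".
- The Statistical methods section fixes the error rate: "significance will be tested using two-sided tests with an alpha level of .05".

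Success is defined as a significant difference on one of the two participation scales. The estimate whose precision is paired with the effect size and power is therefore the difference between arms.

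**The concern.** Power and interval width for the same comparison both depend on one standard error. Once alpha, power and the detectable difference are fixed, the half-width is fixed too. A half-width of 0.36 SD is too small for a design that has only 80% power at 0.7 SD, so the sentence contradicts itself.

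This is the article's only precision statement for the primary outcomes, and it is made twice. A reader will take it that the treatment effect will be estimated to within 0.36 SD either way. If the trial finds no significant difference, the width of the interval determines which effects can be excluded, and on that point the stated figure promises more than 32 effective seniors per group can give.

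**Working it through.** **Inputs.** From Sample size and power calculations: difference 0.7 SD, power 80%, 32 per group before clustering, clustering factors 1.12 and 1.54, dropout 25%. From Statistical methods: two-sided alpha 0.05. Equal allocation is assumed, as the single per-group figure implies. The outcome SD is set to 1.

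**1. The plan's sample size reproduces.**

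- n per group = 2 × (1.96 + 0.8416)² / 0.7² = 32.04. Power at n = 32 is 0.80 by the normal approximation and 0.79 by the t-test.
- 32 × 1.12 / 0.75 = 48 (rounded) and 32 × 1.54 / 0.75 = 66 (rounded).

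The plan's method is therefore the ordinary comparison of two means, and only the precision figure is out of line.

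**2. Half-width implied by the power statement.**

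- Half-width / detectable difference = 1.96 / (1.96 + 0.8416) = 0.70, so the half-width is 0.70 × 0.7 = 0.490 SD.
- The plan's ratio is 0.36 / 0.7 = 0.51.

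The ratio of 0.70 does not involve the sample size, the SD or the clustering factor.

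**3. Half-width calculated directly at 32 per group.**

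| Interval | Formula | Half-width (SD) |
|---|---|---|
| Difference between arms, 95%, normal | 1.96 × √(2/32) | 0.490 |
| Difference between arms, 95%, t on 62 df | t × √(2/32) | 0.500 |
| Difference between arms, 90%, normal | 1.645 × √(2/32) | 0.411 |
| Difference between arms, 80%, normal | 1.28 × √(2/32) | 0.320 |
| Mean of one arm, 95%, normal | 1.96 / √32 | 0.346 |
| Mean of one arm, 95%, t on 31 df | 2.0395 / √32 | 0.3605 |

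Of these, only the one-arm t interval gives 0.36.

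**4. The recruited numbers lead back to the same place.** 48 × 0.75 / 1.12 and 66 × 0.75 / 1.54 both equal about 32.1 effective seniors per group, with a half-width of 0.489 SD (normal) or 0.499 SD (t).

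**5. What a true half-width of 0.36 SD would require.**

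- Effective n per group = 2 × (1.96 / 0.36)² = 59.3 (60.5 with t).
- Recruited per group: 59.3 × 1.12 / 0.75 = 88.5 and 59.3 × 1.54 / 0.75 = 121.7, so about 89 to 122 against the planned 48 to 66.
- Standard error = 0.36 / 1.96 = 0.1837. Power at 0.7 SD = Φ(0.7 / 0.1837 − 1.96) = 0.968.
- Difference detectable with 80% power = 0.36 × 2.80 / 1.96 = 0.51 SD.

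**6. Size of the error.** (0.49 − 0.36) / 0.49 = 27%, or (0.50 − 0.36) / 0.50 = 28% with t.

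**The case against.** Four points can be made for the plan.

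**The figure drives nothing.** The sample size follows from 0.7 SD and 80% power. Success is defined by significance, and no margin or decision rule uses 0.36. This is correct: the error lies in the claim about precision and not in the design. It remains a wrong figure, stated twice as equivalent to the design target.

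**The analysis may be more precise than a simple comparison of means.** The mixed model uses the baseline measurement. A correlation of about 0.68 between baseline and follow-up would bring the half-width at 32 per group down to 0.36 SD. But power at 0.7 SD would then be about 97%, so the two statements would still not be equivalent.

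**The aim is 132 seniors whatever the clustering, so the effective sample may exceed 32 per group.** This is fair. After dropout, 66 × 0.75 = 49.5 seniors remain per group.

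- At a factor of 1.12 the effective number is 44.2 and the half-width 0.42 SD. That factor assumes five seniors per setting, and 132 seniors would then need 132 / 5 = 26.4 settings, more than the planned maximum of 20.
- With 20 settings of 6.6 seniors and five nurses each, there are 1.32 seniors per nurse. The plan's two factors are reproduced by correlations of 0.3 within nurse and 0.3 × 0.10 = 0.03 between nurses of a setting. They give a factor of 1 + 0.32 × 0.3 + 1.32 × 4 × 0.03 = 1.25, an effective number of about 39.5 and a half-width of about 0.44 SD.

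Neither reaches 0.36 SD. These cases do mean that the 27% applies to 32 effective seniors per group and not to every way of filling the 132 places.

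**The one-arm origin is not documented.** This also stands. The article speaks only of the estimate, and the match with the one-arm t interval is an inference. There is another numerical coincidence: 66 per group with factor 1.12 and no dropout gives 0.361 SD. Step (2), however, ties the figure to 32 per group before clustering. The finding does not depend on the origin.

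**Conclusion.** The precision statement is wrong as written. For 32 effective seniors per group, the 95% confidence interval for the treatment difference has a half-width of 0.49 SD (0.50 with t on 62 df). The stated 0.36 SD understates this by about 27%. That 0.36 is not equivalent to 80% power at 0.7 SD follows from the two-sided 5% level and the stated power alone, and holds whatever the sample size, clustering or baseline adjustment. The value 0.49 to 0.50 rests further on equal allocation and on the plan's own 32 per group.

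The claim of about 80% power at 0.7 SD for a single scale tested at 0.05 is not affected, nor are the 48 to 66 per group or the total of 132.

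**What to change.** In the Sample size and power calculations section, replace 0.36 SD by 0.49 SD (or 0.50 SD if the t distribution is used). State that it is the half-width of the 95% confidence interval for the difference between arms with 32 effective seniors per group. The back-reference in step (2) is then correct without further change.

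If the sponsor also decides to split alpha over the two primary scales, which the article does not do, the 97.5% interval would have a half-width of 2.24 × √(2/32) = 0.56 SD and could be given alongside.

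The cost is one corrected number and a less favourable precision claim. Recruitment, conduct and analysis stay as planned. If the sponsor in fact wants a half-width of 0.36 SD for the difference, this correction does not provide it: about 89 to 122 seniors per group would be needed under the plan's own allowances.

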### Statistical methods

Descriptive statistics (mean standard deviation or median and interquartile range) will be used to describe the baseline characteristics of the aged care setting and of the seniors. We will use a linear mixed model to analyze the outcomes and to account for clustering of seniors within nurses within the settings and for repeated measurements. The influence of relevant/prognostic characteristics of aged care setting/seniors on the outcomes will also be investigated by including these as covariates.

The analysis will be based on all the resulting data using the intention-to-treat principle. Moreover, a per protocol analysis and a regression analysis with the adherence to intervention protocol (see below) will be performed to assess the influence of compliance. For all tests, significance will be tested using two-sided tests with an alpha level of .05.

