This trial aims to evaluate the effectiveness of a self-management intervention for DSI seniors living in aged care settings. We chose cluster randomization in order to avoid contamination resulting from the effects of possible exchange of information by nurses within the age care setting. We hypothesize that the intervention group will have a more favorable development in social participation, and in nurses’ job satisfaction than the control group. In addition, we hypothesize that seniors suffering from depressive feelings will benefit more from the intervention, and that intervention outcomes at both the level of the seniors and of the nurses will be associated with the adherence of the nurses to the program.

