## Methods/Design

### Study design

The study is designed as a cluster randomized, single-blind controlled trial (Figure 1). A cluster is defined as an aged care setting with an assigned team of nursing staff. A professional caregiver from the setting who has daily care contact with the participating senior will be linked to that senior; we decided to choose licensed practical nurses as they provide the majority of the daily care in aged care settings in the Netherlands. The seniors in the intervention cluster are offered the Self-Management Program for Dual Sensory Impaired Seniors (SMP-DSI) supported by their own nurse. The seniors in the control cluster are offered usual care. An independent statistician will randomize the settings in blocks using a computer-generated random sequence. Data on self-reported outcome measures will be collected at baseline (T0) and four to six weeks after the intervention is finished (T1).

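### The planned two-time-point mixed model reads most naturally as a comparison of change; adjusting T1 for the T0 score would gain precision at no cost

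*Protocol article*

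**What the plan says.** All of this is in the protocol article.

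- **Statistical methods:** a linear mixed model is to "account for clustering of seniors within nurses within the settings and for repeated measurements". On covariates: "The influence of relevant/prognostic characteristics of aged care setting/seniors on the outcomes will also be investigated by including these as covariates". Neither this sentence nor the control variables in Table 2 name the T0 score of the Hearing Handicap Questionnaire (HHQ) or the Activity Card Sort (ACS). Testing is two-sided at 0.05.
- **Study design:** the self-reported outcomes are measured twice, at T0 and at T1.
- **Background:** the hypothesis is that "the intervention group will have a more favorable development in social participation" than the control group.
- **Sample size and power calculations:** the target is to "detect an effect size of 0.7 or larger with 80% power on either HHQ or ACS". The starting figure is stated so: "Uncorrected for clustering, a sample size of 32 per group is needed for the mentioned effect size and power". For clustering, "the sample size has to be increased by a factor between 1.12" and 1.54.
- **Procedures:** settings are randomised after their seniors have been included.

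**The concern.** A senior with only T0 and T1 has repeated measurements in the model only if T0 is one of the outcomes. Were T0 a covariate, each senior would contribute a single outcome. Together with a hypothesis about development and no T0 score among the covariates, this points to a group-by-time contrast with T0 means free in each arm. With two time points, that contrast is the difference in mean change.

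Such a contrast is valid but spends the T0 data poorly. It subtracts the whole T0 score, where regression would subtract only the part that predicts T1. The sample size, meanwhile, rests on the plain T1 variance, so the planned power and the likely analysis refer to different contrasts. With at most 132 seniors and 25% expected dropout, precision that can be had for nothing is worth taking.

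A second matter is conditional. The article does not say how the clustering terms enter the tested contrast. Setting and nurse effects that are constant over time cancel out of T1 minus T0.

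**Working it through.** **1. The plan's own figures.** Inputs from Sample size and power calculations: effect 0.7 SD, power 80%, two-sided alpha 0.05, five nurses per setting, one or two seniors per nurse, correlations 0.3 and 0.10, dropout 25%.

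- Per group: 2 × (1.96 + 0.84)² / 0.7² = 32.0 (32.04 with unrounded quantiles). The stated 32 is reproduced. The variance used is that of T1 alone.
- Design factor 1 + (m − 1) × 0.3 + m × 4 × 0.03, for m seniors per nurse, taking the setting-level term as 0.3 × 0.10 = 0.03: m = 1 gives 1.12, m = 2 gives 1.54. Both are reproduced.
- Dropout: 32 × 1.12 / 0.75 = 47.8, so 48; 32 × 1.54 / 0.75 = 65.7, so 66. Both are reproduced.

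**2. Variance of the two contrasts.** Take equal variance at T0 and T1 and correlation r. Relative to the plain T1 comparison (= 1):

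- change: 2(1 − r)
- T1 adjusted for T0: 1 − r²
- ratio: 2(1 − r) / [(1 − r)(1 + r)] = 2/(1 + r), which exceeds 1 for every r below 1.

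Change is worse than the plain T1 comparison when 2(1 − r) > 1, that is, when r < 0.5.

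**3. Power.** Power = Φ(0.7 × √(32/(2v)) − 1.96) = Φ(2.8/√v − 1.96), where v is the relative variance and 32 is the effective number per group after the design factor. The values of r are assumed.

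| r | v, change | v, adjusted | ratio | power, change | power, adjusted | effective n per group for 80%: change / adjusted |
|---|---|---|---|---|---|---|
| 0.3 | 1.40 | 0.91 | 1.54 | 66% | 84% | 45 / 30 |
| 0.5 | 1.00 | 0.75 | 1.33 | 80% | 90% | 33 / 25 |
| 0.7 | 0.60 | 0.51 | 1.18 | 95% | 98% | 20 / 17 |

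The standard error of the change contrast is 24%, 15% and 8% larger (√1.54, √1.33, √1.18). The table applies the same design factor to both contrasts, which is a simplification.

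**4. Is T0 as an outcome itself the problem?** No. Generalised least squares with 32 per group and r = 0.5 gives a variance of 0.0625 when the T0 means are free in each arm, which is (2/32) × 2(1 − 0.5). It gives 0.0469 when the arms share one T0 mean, the same as covariate adjustment: (2/32) × (1 − 0.25). The loss comes from leaving the T0 means free.

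**5. Clustering, if only time-constant intercepts were fitted.** The standard error of the change contrast would then carry no design factor.

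- Setting and nurse effects constant over time: change is not clustered and the type I error holds (5.1% in 5,000 simulated null trials, 14 settings × 5 nurses × 2 seniors).
- Change scores carrying the plan's own correlations: 2[1 − Φ(1.96/√1.12)] = 6.4% and 2[1 − Φ(1.96/√1.54)] = 11.4%. Simulated: 6.2% (20 × 5 × 1) and 10.9% (14 × 5 × 2).
- Intermediate cases, 14 × 5 × 2, senior-level T0–T1 correlation 0.6: 8.5% with cluster-level correlation over time of 0.8, and 11.4% with 0.6.

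The simulations tested change scores while ignoring clustering, as a stand-in for the intercepts-only model. All correlations over time are assumptions.

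**The case against.** The strongest reply is that the article describes no model in enough detail to be faulted. It lists no fixed effects, no contrast and no random terms, and a condensed article may leave these to an analysis plan. The study's success criterion is a significant difference on HHQ or ACS, not a difference in change. A joint model with a common T0 mean fits the same sentence and loses nothing. The prognostic covariates might include the T0 score. Even the change contrast is valid, and it reaches 80% power at r = 0.5 and 95% at r = 0.7.

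Much of this stands, and it rules out two stronger readings that a reader might infer.

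- *That putting T0 among the outcomes necessarily wastes baseline information.* Step 4 shows that it does not.
- *That the plan ignores clustering in its primary tests and is therefore anti-conservative.* The article nowhere limits the random part to intercepts, and its stated aim is to account for clustering. Inflation would also need setting or nurse effects that shift between T0 and T1. The article gives no figure for this, and under the null hypothesis the programme itself cannot supply an average shift.

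What the reply does not remove is the direction of the text. Two time points, repeated measurements, a hypothesis about development and no T0 covariate together favour the less efficient contrast. The better one would have to be chosen against that wording.

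**Conclusion.** The point holds as a free improvement in precision, not as an error in a stated model. On the natural reading, the primary contrast has 18% to 54% more variance than a T0-adjusted one for r between 0.7 and 0.3, and it falls short of the planned 80% power if r is below 0.5. The size depends on r, which the article does not give, on equal variance at T0 and T1, and on a common design factor.

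Adjustment is justified because settings are randomised after seniors are included, so T0 means differ between arms only by chance, provided T0 is measured before allocation can affect the scores.

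The clustering part is a conditional safeguard only. Type I error would rise to about 6% to 11% if an intercepts-only model were used and setting or nurse effects changed between T0 and T1. It would stay near 5% if they did not change.

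**What to change.** State the primary analysis of HHQ and of ACS as one of the following:

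- a mixed model of the T1 score, with the T0 score of the same scale as covariate, allocation as fixed effect, and random intercepts for setting and nurse; or
- a joint model of T0 and T1 with one T0 mean common to both arms, and setting-by-time and nurse-by-time random effects.

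Report the adjusted mean difference at T1 as the treatment effect. Under either form, the clustering that the sample size allows for acts on the contrast being tested.

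The cost is a change of wording before the data are analysed. T0 is already collected, and no further data or participants are needed. Seniors with T0 but no T1 add little under either model, so the choice hardly affects the handling of dropout.

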### Process evaluation

In order to assess the internal and external validity of the study, we will evaluate process data on sampling quality (recruitment, randomization and reach) and on intervention quality (relevance, feasibility, adherence and treatment delivery). The data will be performed alongside the SMP-DSI study, and the process evaluation will be executed prior to the effect analysis. Quantitative and qualitative data will be collected from the research database, the intervention diaries and the coaching diaries of the nurses, the semi-standardized records of the trainers, the assessors, the research assistants and the researcher.

To evaluate sampling quality, recruitment and randomization will be defined by description of the recruitment and randomization procedure for the aged care settings; the informed consent and allocation procedure of the seniors; and by description of the barriers and facilitators to the recruiting of the aged care settings, nurses and seniors. Reach will be determined by the proportion of the seniors participating in the SMP-DSI and the number of nurses involved in the intervention.

To evaluate the intervention quality, we will analyze adherence and treatment delivery using data on the frequency and extent to which the SMP-DSI was performed by each pair of senior and nurse, and data on attendance of nurses in the training program. We will also describe the reasons for refusal before the start or during the intervention by aged care setting, nurse and senior. Relevance and feasibility will be defined by the nurses’ diaries and learning goals, the trainers’ training and coaching evaluations, and opinions of the seniors, nurses and trainers about the program. Incentives and barriers toward treatment delivery at the level of aged care settings, nurses and seniors will be classified using the Grol and Wensing framework [38].

